## Abstract

**Background:**

Cycloset™ is a quick-release formulation of bromocriptine mesylate, a dopamine agonist, which in animal models of insulin resistance and type 2 diabetes acts centrally to reduce resistance to insulin- mediated suppression of hepatic glucose output and tissue glucose disposal. In such animals, bromocriptine also reduces hepatic triglyceride synthesis and free fatty acid mobilization, manifesting decreases in both plasma triglycerides and free fatty acids. In clinical trials, morning administration of Cycloset™ either as monotherapy or adjunctive therapy to sulfonylurea or insulin reduces HbA1c levels relative to placebo by 0.55–1.2. Cycloset™ therapy also reduces plasma triglycerides and free fatty acid by approximately 25% and 20%, respectively, among those also receiving sulfonylurea therapies. The effects of once-daily morning Cycloset™ therapy on glycemic control and plasma lipids are demonstrable throughout the diurnal portion of the day (7 a.m. to 7 p.m.) across postprandial time points.

**Methods/Design:**

3,095 individuals were randomized in a 2:1 ratio into a one year trial aimed to assess the safety and efficacy of Cycloset™ compared to placebo among individuals receiving a variety of treatments for type 2 diabetes. Eligibility criteria for this randomized placebo controlled trial included: age 30–80, HbA1c ≤ 10%, diabetes therapeutic regimen consisting of diet or no more than two hypoglycemic agents or insulin with or without one additional oral agent (usual diabetes therapy; UDT). The primary safety endpoint will test the hypothesis that the rate of all-cause serious adverse events after one year of usual diabetes therapy (UDT) plus Cycloset™ is not greater than that for UDT plus placebo by more than an acceptable margin defined as a hazard ratio of 1.5 with a secondary endpoint analysis of the difference in the rate of serious cardiovascular events, (myocardial infarction, stroke, coronary revascularization or hospitalization for or angina or congestive heart failure). Efficacy analyses will evaluate effects of Cycloset™ versus placebo on change from baseline in HbA1c, fasting glucose, body weight, waist circumference, blood pressure and plasma lipids.

**Discussion:**

This study will extend the current data on Cycloset™ safety, tolerability and efficacy in individuals with type 2 diabetes to include its effects in combination with thiazolodinediones, insulin secretagogues, metformin, alpha-glucosidase inhibitors and exogenous insulin regimens.

**Trial registration:**

*clinical trials.gov *NCT00377676

## Background

Reduced insulin-mediated glucose disposal and impaired suppression of endogenous (hepatic) glucose production are dominant metabolic features of the obese state. [1] It has been estimated that 60–80 percent of type 2 diabetic patients are obese. [2] Among representative species of all the major vertebrate classes of animals, the development of obesity and its accompanying insulin resistance has certain adaptive advantages. This adaptation improves survival in times of seasonal famine.[3] Many vertebrate species develop obesity and insulin resistance in preparation for hibernation, migration or during over-wintering periods when food availability is extremely low.[4] Extensive experimental evidence indicates that circadian neuroendocrine rhythms play a pivotal role in the development of seasonal changes in body fat stores and insulin sensitivity. Specifically, temporal changes in the interaction of two distinct circadian neural circadian oscillations, mediated in part by dopaminergic and serotonergic neurotransmitter activity, have been shown to regulate the dramatic seasonal alterations in body weight and body composition that are characteristic of all vertebrate classes from teleosts to mammals.[3] Additional data obtained in pigs and rats suggest that similar mechanisms may play a role in the development of nonseasonal (e.g., aging-related) obesity and insulin resistance.[5,6]

Bromocriptine mesylate, an ergot derivative, is a sympatholytic dopamine D2 receptor agonist that can exert inhibitory effects on serotonin turnover in the central nervous system.[7] Available evidence suggests that bromocriptine can reverse many of the metabolic alterations associated with insulin resistance and obesity by resetting central (hypothalamic) circadian organization of monoamine neuronal activities.[8] Additionally, dopamine agonist treatment reduces ventromedial, arcuate and paraventricular hypothalamic drive for increased hepatic glucose production, lipid synthesis and mobilization, and insulin resistance. [9,10] When administered systemically [11-13] or into the cerebral ventricle [14] during the early hours of the light cycle, bromocriptine prevents or reverses seasonal fattening, insulin resistance and hyperinsulinemia, as well as decreases endogenous (hepatic) glucose production in mammals.

Cycloset™ is a new quick-release oral formulation of bromocriptine mesylate that has been employed in clinical studies to examine the effectiveness of timed bromocriptine administration to humans with metabolic disease including type 2 diabetes. Cycloset™ has been shown to reduce insulin resistance, glucose intolerance and hyperlipidemia during Phase II clinical trials. In three Phase III clinical trials, Cycloset™ significantly improved hyperglycemia among obese individuals with type 2 diabetes [15] Based on these study results, the FDA issued an approvable letter for Cycloset™ for the treatment of type 2 diabetes. Full approval is conditional, in part, on the completion of a large, placebo-controlled, randomized trial in persons with type 2 diabetes to evaluate fully drug-related adverse events with a high degree of certainty. The standard preparation of bromocriptine, Parlodel^®^, has been used for over 25 years in persons with Parkinson's disease, prolactinomas, acromegaly, infertility, and post-partum lactation, many of whom also had diabetes. However, there have been no prospective, randomized, placebo-controlled trials conducted which permit the estimation of incidence rate differences and ratios necessary for ruling out a clinically meaningful increased risk for adverse events in a population of persons with type 2 diabetes. This study will provide data that permits the estimation of serious adverse event incidence rate differences and ratios between Cycloset™ and placebo when these agents are added to usual diabetes therapy. In addition to the evaluation of safety parameters, we intend to evaluate pre-specified efficacy parameters among patient subgroups. Specifically we intend to assess changes in Hba1c among a subgroup of the study subjects that were not adequately controlled on metformin and sulfonylurea therapy. Clinical studies that combined Cycloset™ with metformin were not part of the original Cycloset™ clinical program because metformin was not commercially available in the United States at the time the studies were initiated.

## Methods/Design

### Analysis of safety

The primary objective of the study is to determine in subjects with type 2 diabetes receiving Usual Diabetes Therapy (UDT) and HbA1c ≤ 10%:

1. Whether add-on therapy with Cycloset™ results in all-cause rates of serious adverse events that are not higher than that of placebo by a pre-defined margin.

2. Whether add-on therapy with Cycloset™ results in disease-specific rates of serious cardiovascular adverse events that are not higher than that of placebo by non-inferiority margin of 1.5.

While the primary purpose of this study is to establish the safety profile of Cycloset™ in type 2 diabetes, any potential positive cardiovascular benefits will be evaluated as well.

### Analysis of efficacy

Hba1c changes from baseline to 24 weeks between Cycloset™ and Placebo among subjects with a baseline Hba1c of ≥ 7.5% among the following subgroups:

1. Treated at baseline with any Oral hypoglycemic agent (OHA) including injectable insulin secretagogues

a. Metformin plus or minus one OHA or injectable insulin secretagogue

b. Sulphonylurea plus or minus one OHA or injectable insulin secretagogue

2. Treated at baseline with Metformin and one sulphonylurea

### Study design and setting

This is a double blind, multi-center, placebo-controlled, parallel group, non-inferiority study in subjects with type 2 diabetes, comparing usual diabetes therapy (UDT) plus Cycloset™ to UDT plus placebo. Following a two-week lead-in period, 3,095 subjects were randomized in a 2:1 ratio to UDT plus Cycloset™ or UDT plus placebo across 73 clinical centers in the United States and Puerto Rico. Subjects were expected to remain on study treatment for 12 months, the first six weeks of which constitute a dose titration period.

#### Ethical considerations

Full ethical approval for this study was obtained. An external Data Monitoring and Safety Committee monitored the study progress.

#### Study interventions

The experimental condition is Cycloset^® ^in addition to the subject's current diabetes therapeutic regimen and lifestyle regimen. The control condition is placebo subject's current diabetes therapeutic regimen and lifestyle regimen. The regimen must consist of either diet, oral hypoglycemic agents (no more than 2), or insulin (alone or with no more than 1 oral hypoglycemic agent). The usual diabetes agents could not change during the first three months of the study. However, the dosages of the oral agents or insulin were modified as deemed appropriate by the study site investigator to achieve target glycemic goals recommended by the American Diabetes Association [16] After three months, alterations in the diabetes regimen were allowed if deemed necessary by the study site investigator to adhere to the ADA guidelines for achieving glycemic control. Prior to switching oral anti-diabetic medication to an alternative anti-diabetic medication, titration of the current oral anti-diabetic medication up to maximum tolerated dose was preferred and recommended to the study site investigators. However, the change in the regimen could not include additions that resulted in a final regimen that exceed two oral agents (not including study medication), or insulin, plus one oral agent (not including study medication).

#### Identification of eligible patients

Patients meeting the inclusion criteria were identified by research centers across the United States which included nineteen centers from the Veteran Affairs Healthcare System.

#### Confirmation of serious adverse events

Study site investigators elicited information regarding serious adverse events. The study safety officer reviewed all relevant safety data obtained from the study sites. Narratives were written from source documents. All serious adverse events (SAE) were verified for accuracy of coding for inclusion in the database. All SAEs were reviewed by an external adjudication committee consisting of three physicians (two cardiologists and one endocrinologist). Whenever possible, the medical records corresponding with the event were also reviewed.

#### Determining eligibility for the study

The principle investigator at each site reviewed the screening laboratories and medical history and assessed eligibility of screened study subjects (see table 1 inclusion and exclusion criteria).

**Table 1 T1:** Inclusion/Exclusion Criteria

**Inclusion**	*Criteria*
Diagnosis Type 2 Diabetes	*≥ 6 months prior to enrollment*
Age	*30–80 years*
Hba1c at screening	*≤ 10*
Male or Female	*Female of child bearing age must use definitive contraceptive therapy*

***Exclusion***	

Taken Prescription sympathomimetic	*Taken seven days prior to screening*
Drugs not permitted during study	*Ergot alkaloid derivatives, or anti-migrane medications*
History of alcoholism or drug abuse	*Within 3 years of study entry*
Donation of blood	*30 days prior to study entry*
Has received any experimental drug or used an experimental device	*Within 30 days of study entry*
Pregnant or lactating women	
Known hypersensitivity to any of the formulation components	
***Subjects with clinically significant major organ system disease:***	
**• seizure disorder,**	
**• significant gastroparesis or orthostatic hypotension (autonomic neuropathy),**	
**• cerebrovascular accident in the previous 6 months,**	
**• uncontrolled hypertension (systolic BP >160 or diastolic BP > 100 at screening)**	
**• coronary artery bypass graft or coronary angioplasty in the previous 3 months, myocardial infarction in the previous 6 months, or unstable angina pectoris (chest pain at rest, worsening chest pain, or admission to the ER or hospital for chest pain) within the previous 3 months,**	
**• congestive heart failure defined by NYHA as Class III or IV**	
**• clinical nephrotic syndrome, or renal impairment with a serum creatinine > 1.4 mg/dl if female receiving treatment with metformin, > 1.5 mg/dl if male receiving treatment with metformin, and > 1.6 mg/dl in not on metformin,**	
**• impaired liver function, including having AST or ALT greater than three times the upper limit of normal,**	
**• active infection (e.g., HIV, hepatitis), or a history of severe infection during the 30 days prior to screening,**	
**• major surgical operation during the 30 days prior to screening,**	
**• cancer, other than non-melanoma skin or non metastatic prostate cancer within the past 5 years**	
**• Any concurrent illness, other than diabetes mellitus, not controlled by a stable therapeutic regimen.**	
**• Working rotating, varying or night shifts**	
**• Patients taking unapproved herbal supplements that may be associated with a risk of cardiovascular events (such as ephedra, yohimbe etc)**	
**• Patients who have started therapy with an erectile dysfunction drug within 2 weeks prior to screening; patients may not begin treatment with an erectile dysfunction drug during the study period; patients previously taking erectile dysfunction drugs should do so only under medical supervision.**	
**• Subjects with circumstances or abnormalities (e.g., blindness or a history of non-compliance) that would interfere with the interpretation of safety or efficacy data or completion of the study.**	

#### Patient follow-up procedures

After screening, patients were randomized and titrated to the maximum tolerated dose of the study drug over a six week period. After titration, subjects were seen every 3 months until study end (week 52) or early termination. Subjects were contacted 30 days after completion of study drug to record any adverse events occurring after treatment completion. See table 2 for visit schedule and assessments.

**Table 2 T2:** Study Flow Sheet

			**STUDY WEEK**												
		-2	-1	0	1	2	3	4	5	6	12	24	36	52	Termination^3^

Assessment and Measurement	Pre-Screen	Screen	♠												

HbA1c: Local lab < 10	♣	♣													
Clinic Visit		X		X			X			X	X	X	X	X	X
Medical History		X													
Concomitant Meds and Illnesses		X					X			X	X	X	X	X	X
Pregnancy test*		X													
Full Physical Exam, *(Weight & Waist Circumference)*^1^		X										X		X	X
Blood pressure		XX		X			X			X	X	XX	X	X	X
Record Adverse events (AE)				X			X			X	X	X	X	X	X
ECG		X										X		X	X
Telephone Call to Subject for AE's Reports					X	X		X	X						
CBC & Plasma Sample		X										X		X	X
Chemistry, LAE♥		X^⊕^								X		X		X	X
HbA1c		X									X	X	X	X	X
Fasting Plasma Glucose^2^		X		X			X			X	X	X	X	X	X
Fasting Lipid Profile^♦2^		X										X		X	X

Notes on measures

♣ Local lab documentation of HbA1c ≤ 10 must be confirmed within 12 wks prior to conducting the Week-2 screening visit tests

♠ During Week-1 any labs or tests unable to be performed at screening should be completed

* To include pregnancy test (beta-HCG) in women of childbearing potential.

♥ CBC with differential and platelets, urinalysis, liver function (ALT, AST, alkaline phosphatase and total bilirubin), BUN, creatinine, Na, K, Cl, bicarbonate, calcium, phosphorus, and albumin.

♦ Total cholesterol, triglycerides, HDL-cholesterol, and LDL-cholesterol.

1. for body mass index and waist circumference to be measured on subject in the supine position at the level of the umbilicus

2. for BMI Obtained in the morning after a minimum 8 h overnight fast

3. A full 52-week assessment must be performed whenever a subject *terminates *the study early.

#### Patient outcome measures

##### Safety outcomes

Primary – all cause serious adverse events

Secondary – Composite of cardiovascular outcomes (myocardial infarction, hospitalized angina or congestive heart failure, stroke, or coronary revascularization)

##### Additional safety parameters

All adverse events, withdrawal due to an adverse event, laboratory values, vital signs and ECG

##### Other clinical measures

• Fasting lipid profile (total, LDL, HDL cholesterol, triglycerides) and

• HbA1c and

• Fasting plasma glucose level and

• Body weight, waist circumference, blood pressure

#### Sample size considerations

##### Sample size calculation for all-cause serious adverse events

In order to test the primary hypothesis at a one-sided alpha = .05 and have a power of 1-β = 0.90 when the non-inferiority margin is 1.5, the total number of subjects with all-cause serious adverse events that must be observed during the study is 235 with a sample size of 2,991 (assuming the placebo rate of 0.08).

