##### Power calculation for serious cardiovascular adverse events

In order to test the hypothesis for serious cardiovascular adverse events as for the primary endpoint at a one-sided alpha = .05 when the non-inferiority margin is 1.5, the final sample size of 3000 to 3300 subjects will provide at least 62% power, assuming a hypothetical rate of events of 3.43%, or 103 to 113 cardiovascular serious adverse events.

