### Statistical analysis – safety and other clinical measures

#### Safety

The Intention-To-Treat (ITT) analysis set will include all subjects who were randomized to the study and received at least one dose of study treatment (either Cycloset™ or placebo) and will be used for evaluating all safety endpoints. The Evaluable Per-Protocol (EPP) analysis set will consist of those ITT subjects with no major protocol violations and with at least one post-randomization measurement of HbA1c, fasting plasma glucose, lipids, weight, waist circumference or blood pressure. The primary analysis tested the hypothesis that the occurrence of all-cause serious adverse events for Usual Diabetes Therapy (UDT) plus Cycloset™ is not inferior to that for UDT plus placebo by a predefined margin. For this study, the predefined margin of non inferiority was defined as a hazard ratio (UDT plus Cycloset^® ^versus UDT plus placebo) of 1.5. The hazard ratio and one-sided 96% confidence interval will be obtained from the Cox regression model with treatment and center effects. The non-inferiority will be supported by the result that the upper bound of the confidence interval is below 1.5. The proportional hazards assumption underlying the Cox model will be examined with appropriate alternative statistical models applied. Results based on the ITT analysis set will be considered primary and those based on EPP analysis supportive. The secondary safety endpoint is the time to the occurrence of first cardiovascular SAEs (myocardial infarction, stroke, in-patient hospitalization for heart failure, angina or revascularization surgery). These endpoints will be analyzed in the same manner as described above for the primary endpoint

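### The safety endpoints are sized at one-sided alpha 0.05 but tested with a one-sided 96% bound (alpha 0.04), and nothing reconciles the two levels

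*Protocol article*

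**What the plan says.** **Sample size, all-cause serious adverse events.** The level and power are "In order to test the primary hypothesis at a one-sided alpha = .05 and have a power of 1-β = 0.90", with a margin of 1.5. The result is that "the total number of subjects with all-cause serious adverse events that must be observed during the study is 235", in 2,991 subjects, with a placebo rate of 0.08.

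**Power, serious cardiovascular adverse events.** The test is described "as for the primary endpoint at a one-sided alpha = .05 when the non-inferiority margin is 1.5". The article states that "the final sample size of 3000 to 3300 subjects will provide at least 62% power". Behind this figure stands an event rate of 3.43%, which it converts to between 103 and 113 events.

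**Statistical analysis, Safety.** "The hazard ratio and one-sided 96% confidence interval will be obtained from the Cox regression model with treatment and center effects". Non-inferiority is supported if the upper limit lies below 1.5. The same section applies this method to the first cardiovascular serious adverse event.

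**Study design and setting.** 3,095 subjects were randomized 2:1.

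The article mentions an external monitoring committee under Ethical considerations. It describes no interim analysis, alpha spending or multiplicity adjustment that would turn 0.05 into 0.04.

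**The concern.** A non-inferiority test that compares a one-sided 96% upper limit with the margin has a type I error of 0.04, not 0.05. The article therefore gives two levels for its primary claim, and the same two for the cardiovascular claim. Either the analysis section misstates the bound, or the two sample-size paragraphs describe a different test from the one that will be run.

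The stake is the pass/fail rule. The Background says that full approval depends in part on a large randomized safety trial of this kind. A result that falls between the two thresholds would be non-inferior under one section and not under the other. The sub-study efficacy section indicates that the data were still blinded, so the level can still be settled without knowledge of the result. Settled later, it would be a post hoc choice of success criterion.

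**Working it through.** **Inputs from the article.** Margin 1.5, so ln 1.5 = 0.4055 and its square is 0.1644. Allocation 2:1, so the information factor is (2/3)(1/3) = 2/9. Power 0.90, so z = 1.2816. One-sided z is 1.6449 at alpha 0.05 and 1.7507 at alpha 0.04. Stated events are 235 (primary) and 103 to 113 (cardiovascular).

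**Assumption.** The true hazard ratio is 1. The article does not state it, but the match below supports it.

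**Formulas (Schoenfeld).**
- Events needed: D = (z_alpha + z_power)² / [(2/9)(ln 1.5)²]
- Power with D events: Φ(√(2D/9) × ln 1.5 − z_alpha)
- Largest observed hazard ratio that passes: 1.5 × exp(−z_alpha / √(2D/9))

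**Step 1: reproduce the stated figures at 0.05.**
- Events: (1.6449 + 1.2816)² / (0.2222 × 0.1644) = 234.4, rounded up to 235. This matches.
- Power at 235 events: Φ(2.930 − 1.645) = 90.1%. This matches.
- Cardiovascular power: Φ(1.940 − 1.645) = 61.6% at 103 events and Φ(2.032 − 1.645) = 65.1% at 113. The lower value rounds to the stated 62%.

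Other formulas at 0.05 do not give 235: 1:1 Schoenfeld gives 209, 1:1 Freedman 215, and 2:1 Freedman 210 or 274. A 1:1 Schoenfeld calculation at 0.04 happens to give 62.1% cardiovascular power at 103 events. It does not explain the figures, because the trial is 2:1, the paragraph names 0.05, and the same calculation gives 224 primary events.

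**Step 2: the same formulas at 0.04, as a single final test.**

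| Quantity | alpha 0.05 | alpha 0.04 |
|---|---|---|
| Events for 90% power | 235 (234.4) | 252 (251.7) |
| Power at 235 events | 90.1% | 88.1% |
| Power at about 248 events | 91.4% | 89.6% |
| Cardiovascular power, 103 events | 61.6% | 57.5% |
| Cardiovascular power, 113 events | 65.1% | 61.1% |
| Events for 62% cardiovascular power | 105 | 116 |

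The 248 events are 3,095 × 0.08 = 247.6, with 8% in both arms. The article's own ratio is 235/2,991 = 7.86%. On that ratio, 252 events correspond to 252 × 2,991/235, or about 3,207 subjects.

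**Step 3: the two pass thresholds.**

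| Events | Largest passing HR, 95% bound | Largest passing HR, 96% bound |
|---|---|---|
| 235 | 1.195 | 1.177 |
| 103 | 1.064 | 1.040 |
| 113 | 1.080 | 1.058 |

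For 235 events: √(2 × 235/9) = 7.226, so 1.5 × exp(−1.6449/7.226) = 1.195 and 1.5 × exp(−1.7507/7.226) = 1.177.

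**The case against.** The strongest reply is that the article does not show why 96% appears. Two explanations fit.

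- **A misprint for 95%.** Then the sample-size paragraphs are right as they stand, and only the analysis sentence is wrong.
- **A deliberate adjustment,** for instance alpha used at a monitoring look, with the detail in a full protocol or analysis plan that is not shown. Then the single-test powers at 0.04 may not apply either, because overall power includes the chance of an early claim. As an illustration only (the article describes no such look), take one look at half the information, a final level of 0.04 and an overall level of 0.05. Overall power is then 88.8% at 235 events, 90.2% at 248, and 59.4% to 62.9% for 103 to 113 cardiovascular events. On that design the stated 62% is not missed over the whole range.

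This limits what can be said about power. It does not remove the contradiction: both levels are printed, and one of them needs correcting or explaining. An unseen document does not make the two statements agree.

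It can also be said that the effect is small and on the safe side. Only the analysis section gives an operative pass/fail rule, and it is the stricter of the two, so a claim made under it does not inflate type I error. With 3,095 randomized and 8% in both arms, primary power at 0.04 is only 0.4 points below 90%. All of this stands.

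A reader might go further and infer that the stricter bound means the trial will not deliver its stated event count. That does not follow: the confidence level has no influence on how many events accrue, only on how many are needed for 90% power.

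**Conclusion.** The inconsistency is real and bears on the primary decision rule: 0.05 in both sample-size paragraphs, 0.04 in the analysis, and nothing that joins them. The stated figures belong to 0.05.

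If the analysis is a single test at 0.04, the requirement for 90% power rises by 17 events (252 against 235, about 7%). The loss of primary power is 2.0 points at 235 events, and most of the shortfall from 90% is offset if 8% holds in both arms of the 3,095 randomized. Cardiovascular power falls by about 4 points and is below the stated 62% across the whole event range.

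These sizes rest on the Schoenfeld approximation, a true hazard ratio of 1, and one final analysis. A reader might conclude that the cardiovascular power statement is simply false, or that the primary endpoint is materially underpowered. The article supports neither: the first depends on 96% being intended and tested once, and the second is not borne out by the numbers. What is certain is that the pass threshold has two values, 1.195 and 1.177 at 235 events, and that a result between them has no defined outcome.

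**What to change.** Before unblinding, state one level in the two sample-size paragraphs and in the Safety analysis section.

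- **If 96% is a misprint,** change the analysis to a one-sided 95% bound. The 235 events, 90% power and 62% cardiovascular power then stand.
- **If 96% is intended as a single test at 0.04,** say why it differs from 0.05, and restate 252 events for 90% power, 88% power at 235 events, and 57% to 61% for the cardiovascular endpoint.
- **If alpha was used at an interim look,** describe the look and the spending, and recompute the event requirement and both powers for that design. The single-test figures should not be used.

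The cost is a change of wording and, if 96% is kept, a short recalculation. No conduct of the trial changes. The only downside of keeping 96% is slightly less favourable stated power.
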